## Abstract

**Background:**

Recent evidence underscores the utility of rapid-acting antidepressant interventions, such as ketamine, in alleviating symptoms of major depressive episodes (MDE). However, to date, there have been limited head-to-head comparisons of intravenous (IV) ketamine infusions with other antidepressant treatment strategies in large randomized trials. This study protocol describes an ongoing multi-centre, prospective, randomized, crossover, non-inferiority trial comparing acute treatment of individuals meeting diagnostic criteria for a major depressive episode (MDE) with ketamine and electroconvulsive therapy (ECT) on efficacy, speed of therapeutic effects, side effects, and health care resource utilization. A secondary aim is to compare a 6-month maintenance strategy for ketamine responders to standard of care ECT maintenance. Finally, through the measurement of clinical, cognitive, neuroimaging, and molecular markers we aim to establish predictors and moderators of treatment response as well as treatment-elicited effects on these outcomes.

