#### Crossover phase

Participants only enter the crossover phase if they do not meet antidepressant response criteria at the end of the randomized treatment phase. During the crossover phase, ECT non-responders receive a course of 9 or 12 ketamine infusions, while ketamine non-responders undergo 9 or 12 ECT sessions. Non-responders at the end of the crossover phase exit the study. Those meeting the response criteria after the crossover phase (≥ 50% MADRS score decrease relative to pre-crossover score and MADRS score < 22) may enter the maintenance phase.

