#### Maintenance phase

Treatment during the maintenance phase lasts 6 months from entry (immediately after completion of the randomized treatment or crossover phase), with a follow-up assessment at month 7. ECT maintenance follows standard of care wherein the treating physician will determine if the participant will receive ECT maintenance, and if so, the frequency of these treatments in accordance with patients’ needs and Canadian Network for Mood and Anxiety Treatments (CANMAT) 2016 Clinical Guidelines [15]. Participants undergoing ketamine maintenance treatment receive infusions according to the following schedule: 1 infusion per week for the first 4 weeks, followed by 1 infusion every 2 weeks for 2 months, and then 1 infusion every month for 3 months. Individuals who experience a relapse of depressive symptoms (MADRS ≥22 or loss of 50% improvement from baseline) with monthly ketamine infusions may return to bi-weekly infusions for the remainder of the maintenance phase. Participants who fail to meet response criteria at any two consecutive study visits during the maintenance phase discontinue treatments (if present) and exit the study. At the conclusion of study participation, all participants have a final follow-up visit and are discharged to their referring physician with treatment recommendations.

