Speed of therapeutic effects is defined as the number of treatments required for participants to first meet antidepressant response criteria. A Kaplan-Meier survival analysis will be used to compare the mean number of required treatments for first response to ECT and ketamine during the randomized treatment phase. Side effect burden will be quantified by summing the total frequency and severity scores of the TSES administered after the final treatment during the randomized treatment phase. Mean total TSES scores for ECT and ketamine will be compared using an ANOVA (appropriate covariates will be included). Further, side effect profiles for each treatment will be derived by identifying the most common side effects reported in each arm of the trial (present in > 5% of participants). Treatment tolerability will be estimated via dropout rates. Finally, data from CNS Vital Signs will permit comparison of any cognitive side effects associated with ECT or ketamine (compared at the end of the randomized treatment phase). Level of health care utilization (estimated using average cost of treatment administration, number of days of inpatient hospitalization, and frequency of outpatient consultations) associated with ECT and ketamine will be compared using ANOVAs.

The main outcome in the maintenance phase will be time to relapse. Due to differences in the administration schedules of ECT and ketamine during maintenance, two parallel descriptive statistics will be outlined. For each treatment, mean time to relapse (loss of antidepressant response) will be estimated using Kaplan-Meier survival analysis.

While data from each analytical platform will be analyzed independently using the methods described herein and elsewhere [21], integration of data collected across platforms will also be carried out, and will be overseen by the CAN-BIND Data Science Advisory Team comprised of Principal Investigators, domain-specific informatics advisors, and operations support. In addition to conventional statistical approaches, machine-learning approaches will be applied particularly with regards to outcome prediction (i.e., response/non-response to ECT and ketamine at 3 or 4 weeks of treatment).

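### The maintenance summary is a Kaplan-Meier mean time to relapse with no truncation time in a 6-month phase, and the relapse reference score for crossover responders is not settled

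*Protocol article*

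**What the plan says.** The Data analyses section makes time to relapse the main maintenance outcome and fixes its summary: "For each treatment, mean time to relapse (loss of antidepressant response) will be estimated using Kaplan-Meier survival analysis". Because the two administration schedules differ, "two parallel descriptive statistics will be outlined". No contrast between treatments is planned.

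The Maintenance phase section sets the window: "Treatment during the maintenance phase lasts 6 months from entry", "with a follow-up assessment at month 7".

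Three places bear on the relapse event:

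- **Crossover phase.** Response, and so entry to maintenance, requires a 50% "MADRS score decrease relative to pre-crossover score", together with a score below 22.
- **Maintenance phase.** Relapse is given in parentheses as "MADRS ≥22 or loss of 50% improvement from baseline", in a sentence about patients on monthly ketamine infusions who may return to infusions every two weeks. The Clinical platform section explains baseline as the time before the randomized treatment phase.
- **Data analyses.** Relapse is loss of antidepressant response, with no reference score named.

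The abstract states the aim as "A secondary aim is to compare a 6-month maintenance strategy for ketamine responders to standard of care ECT maintenance". The Background section of the main text asks only whether ketamine response can be sustained as infusions are spaced out.

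**The concern.** A mean survival time is the whole area under the survival curve. Patients who finish maintenance without relapse are censored at the end of follow-up, and the area beyond that point is unknown. A figure labelled mean time to relapse would in fact be the mean up to wherever observation stopped. It cannot exceed about 6 to 7 months, however durable the response is. Readers would take it for a measure of durability.

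The second issue is the event itself. For first-phase responders, entry and relapse use the same reference score. For crossover responders they may not, so the date of relapse, or whether relapse occurred at all, can depend on which section the analyst follows.

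**Working it through.** The plan states no relapse rate, event count or expected mean for maintenance, so there is no figure of its own to reproduce.

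**1. The mean**

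Inputs: 6-month treatment and a month-7 visit (Maintenance phase section). Assumed: a constant relapse hazard, with a proportion r relapsing by 6 months, r = 0.30, 0.50 or 0.70.

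Formulas: λ = −ln(1 − r)/6; unrestricted mean = 1/λ; mean restricted to time τ = (1 − e^(−λτ))/λ. At τ = 6 the restricted mean equals r/λ.

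| r by 6 months | λ per month | Unrestricted mean (months) | Restricted to 6 | Restricted to 7 |
|---|---|---|---|---|
| 0.30 | 0.0594 | 16.8 | 5.05 | 5.73 |
| 0.50 | 0.1155 | 8.7 | 4.33 | 4.80 |
| 0.70 | 0.2007 | 5.0 | 3.49 | 3.76 |

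- Between 30% and 50% relapse, the unrestricted means differ by 16.82 − 8.66 = 8.2 months. The 6-month restricted means differ by 5.05 − 4.33 = 0.72 months.
- Moving the horizon from 6 to 7 months changes the 50% case from 4.33 to 4.80, so the printed value depends on a choice that the text does not state.
- A third reading, the mean among those who relapse by 6 months, is 1/λ − 6(1 − r)/r. This gives 2.8, 2.7 and 2.4 months for r = 0.30, 0.50 and 0.70.
- The curve is very unlikely to reach zero. With an assumed 50 entrants, all followed to 6 months, the chance that every one relapses is 0.70^50 = 1.8 × 10⁻⁸ at 70% relapse. It is 0.90^50 = 0.5% even at 90%.

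**2. The reference score**

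Take the relapse parenthesis as the survival event, and read it as improvement from baseline falling below 50% or a score of 22 or more.

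- *Patient who worsened before crossover:* baseline 30, pre-crossover 36, score 17 after crossover. Against the pre-crossover score, (36 − 17)/36 = 52.8% and 17 is below 22, so the patient may enter maintenance. Against baseline, (30 − 17)/30 = 43.3%, so the patient already meets the relapse rule.
- *Patient who improved somewhat before crossover:* baseline 36, pre-crossover 30. Half of 30 is 15 and half of 36 is 18. Scores of 16 to 18 are non-response against the pre-crossover score but not relapse against baseline.
- *First-phase responders:* both rules refer to baseline, so there is no conflict.

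The Maintenance phase section also has an exit rule based on two consecutive visits without response. The text does not say whether the event is dated at the first or the second such visit.

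**3. Aim and analysis**

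The abstract says compare; the Data analyses section describes each treatment separately. Those entering maintenance are responders, selected after randomization, from either the randomized or the crossover phase. On the ECT side, the physician decides whether any maintenance ECT is given.

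**The case against.** The best defence of the mean is that both groups share one 6-month phase and one month-7 visit. An area under the curve stopped at the last observation would then be close to a restricted mean in each group, and a journal article may leave the horizon to an analysis plan that is not shown. The first part stands: a restricted mean can be estimated, and a reader who infers that nothing can be estimated from this phase goes too far. But the article does not simply leave the summary open. It names a mean, without restriction, for a censored outcome. An analysis plan that follows it would have to choose the horizon, and the choice changes both the value and its meaning, because the seventh month lies after the treatment phase.

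On the reference score, a reader might infer that the protocol itself declares some patients relapsed on the day they enter. It does not. The baseline-referenced wording is attached to patients on monthly ketamine, which begins only after the weekly and two-weekly infusions, and it governs a change of schedule. The analysis section could be read as loss of the response that qualified the patient, which would remove the overlap at entry. What remains is that the text does not say which reading applies.

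On the comparison, a reader might infer that an invalid between-strategy comparison is planned. None is. The Data analyses section is openly descriptive, and the mismatch comes down to one verb in the abstract. Nor does that section say outright that randomized-phase and crossover responders will be pooled; it only gives one estimate for each treatment.

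**Conclusion.** The point holds in three parts of unequal weight.

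1. **Main part.** The unrestricted Kaplan-Meier mean is not identified unless everyone relapses within follow-up, and the printed value would be fixed largely by the follow-up length. The sizes above rest on a constant hazard and on assumed 6-month relapse of 30% to 70%. The cap at about 6 to 7 months needs neither assumption.
2. **Second part.** The relapse reference is inconsistent across the Crossover phase, Maintenance phase and Data analyses sections, for crossover responders only. Relapse at entry arises only if the maintenance wording is used as the survival event and the pre-crossover score exceeds baseline. The documents do not show how many patients that would be.
3. **Minor part.** The abstract's aim does not match the descriptive analysis or the objective in the main-text Background.

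The primary outcome and its analysis are not affected. The change should be made because it concerns the outcome that the plan itself calls the main one for maintenance.

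**What to change.** - In Data analyses, replace the mean with two summaries for each treatment: the Kaplan-Meier relapse-free proportion at 6 months, and the mean time to relapse restricted to a stated 6-month horizon common to both treatments. Give both with 95% intervals, and show randomized-phase and crossover responders separately.
- Reconcile the Crossover phase, Maintenance phase and Data analyses sections on the reference score for crossover responders, and state at which visit the event is dated, before the relapse variable is derived. Which reference applies is for the investigators to settle.
- Reword the abstract's secondary aim to agree with the descriptive analysis and with the objective in the main-text Background.

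The cost is wording and analysis specification. No new data or visits are needed. Showing the two responder groups separately will widen their intervals.

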Each participant undergoes 2 or 3 imaging sessions: 1) at baseline, prior to treatment initiation, 2) after 3 or 4 weeks of randomized treatment, and 3) for responders, at the mid-point of maintenance (after approximately 4 consecutive months of treatment). During each session, structural MRI, resting-state functional MRI (rs-fMRI), and diffusion tensor imaging (DTI) data are acquired, consistent with established CAN-BIND imaging protocols [42]. In brief, a T1 scan is first acquired (TR = 1760 ms, TE = 2.19 ms, slice thickness = 1 mm, FOV = 256 mm, flip angle = 15, sagittal acquisition, GRAPPA on); a T2-weighted BOLD EPI scan is then obtained while participants look at a fixation cross (TR = 2500 ms, TE = 30 ms, slice thickness = 3 mm, FOV = 210 mm, flip angle = 83, GRAPPA on, acceleration factor PE = 2, acquisition: interleaved). This is followed by DTI acquisition (TR = 8000 ms, TE = 94 ms, GRAPPA: on, acceleration factor PE = 2, 30 directions at 2 b-values:1 and 1000 s/mm^2^; monopolar diffusion, voxel size: 2.5mm^3^, 58 slices, orientation: transverse, FOV = 240 mm). An additional multi-echo magnetization prepared-rapid gradient echo (ME-MPRAGE) sequence has been added to the CAN-BIND imaging protocol across most sites for higher resolution structural images (TR = 1760 ms, TE1/2/3/4 = 1.69/3.55/5.41/7.27 ms, slice thickness = 1 mm, FOV = 256 mm, flip angle = 7, sagittal acquisition, GRAPPA on, acceleration factor PE = 2). Finally, at the Ottawa and Montreal sites, proton magnetic resonance spectroscopy (^1^H-MRS) data are acquired from the dorsal anterior cingulate cortex to measure glutamate + glutamine (Glx) (Point RESolved Spectroscopy [PRESS]; TR = 2000 ms, TE = 30 ms; voxel, water suppression BW: 70 Hz, averages: 128, 40 × 20 × 15 mm). Neuroimaging is being conducted to identify potential predictors of response and non-response, and examine changes in brain features with acute and longer-term treatment.

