### Data analyses

The primary outcome measure is the rate of antidepressant response (i.e., percentage of participants meeting antidepressant response criteria [≥ 50% reduction in MADRS scores from baseline and MADRS score < 22]) in each arm at the end of the randomized treatment phase. A total of 240 participants will be enrolled into the randomized treatment phase across the four recruiting sites. This will allow for a 20% drop-out rate (i.e., withdrawal of approximately 40 participants), resulting in a total sample of *N* = 200. For the primary efficacy analyses, a non-inferiority margin of 20% was selected based on clinical judgment. Thus, a sample of 200 participants (*N* = 100/treatment arm) is required to be 90% certain that the upper limit of a one-sided 95% confidence interval will exclude a difference in favour of the ECT group of more than 20%. Secondary efficacy outcomes will include percent change in MADRS scores from baseline to the end of the randomized treatment phase, and remission rates (MADRS score ≤ 10). Response and remission rates will also be assessed for the crossover phase. Clinical scores will be analyzed using linear mixed models (appropriate covariates, such as site, will be included, as needed). Categorical outcomes (response/remission) will be examined using χ^2^ tests. The alpha will be set at 0.05.

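### The machine-learning prediction target is fixed as response/non-response, a cut of the MADRS, although the continuous end-of-phase score is collected and would carry more information

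*Protocol article*

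**What the plan says.** The last paragraph of Data analyses plans machine learning for outcome prediction and spells out the target: "outcome prediction (i.e., response/non-response to ECT and ketamine at 3 or 4 weeks of treatment". The sentence opens: "In addition to conventional statistical approaches, machine-learning approaches will be applied particularly with regards to outcome prediction". Just before it, the same paragraph says that "data from each analytical platform will be analyzed independently using the methods described herein and elsewhere".

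Earlier in Data analyses, response is defined as "≥ 50% reduction in MADRS scores from baseline and MADRS score < 22". The continuous scale also appears there, but as an efficacy outcome: "Secondary efficacy outcomes will include percent change in MADRS scores from baseline to the end of the randomized treatment phase". Linear mixed models are planned for clinical scores. Neither is linked to prediction.

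The aim itself is put in general terms. The Abstract says "we aim to establish predictors and moderators of treatment response", and the Neuroimaging platform section says "Neuroimaging is being conducted to identify potential predictors of response and non-response". Neither sentence fixes a measurement scale.

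**The concern.** Once the target is binary, a patient who improves by 48% is labelled the same as one who does not improve at all, and a patient who improves by 52% the same as a full remitter. The trial needs the cut for its primary endpoint and for deciding who crosses over and who enters maintenance. Neither use requires that prediction models be trained on it.

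Prediction and moderation form a stated aim, resting on roughly 100 patients per arm and on imaging, transcriptomic, methylation, cytokine and cognitive features. A lossy target means that real predictors and treatment-by-marker moderators are missed more often, and that patients close to the cut receive unstable labels.

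**Working it through.** **Inputs from the protocol article**
- Analysed sample: 200, or 100 per arm (Data analyses). The plan describes this as 20% dropout from 240, with about 40 withdrawals. Strictly, 20% of 240 is 48, which leaves 192; the efficiency ratios below do not depend on this.
- Response range for ECT: 50-80% (Background). No planning rate is given for either arm.
- Entry MADRS: at least 26 (Table 1).

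**Assumptions added here**
- Normal latent improvement with a single cut, one linear marker, two-sided 5% test.

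**The plan's own figure.** The article gives no sample size or power for prediction. Its only figure is 100 per arm for the non-inferiority test (20-point margin, one-sided 5%, 90% power). With equal response rates p, n per arm = 2p(1-p)(1.645+1.282)²/0.20², which gives 103 at p = 0.60 and 98 at p = 0.65. The figure is therefore reproduced at those rates, and 100 per arm is a fair basis for what follows.

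**Is response a single cut?** Half of any baseline from 26 to 43 is at most 21.5, already below 22. The second threshold binds only from a baseline of 44, where half is 22. For lower baselines the criterion is a single cut on percent change.

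**Relative efficiency of the cut.** With response proportion p and z_p the normal quantile, k² = φ(z_p)²/[p(1-p)].

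| p | φ(z_p) | k² | Information lost | 200 participants are worth |
|---|---|---|---|---|
| 0.50 | 0.3989 | 0.637 | 36% | 127 |
| 0.60 | 0.3863 | 0.622 | 38% | 124 |
| 0.70 | 0.3477 | 0.576 | 42% | 115 |
| 0.80 | 0.2800 | 0.490 | 51% | 98 |

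Example at p = 0.70: 0.3477²/(0.70 × 0.30) = 0.1209/0.21 = 0.576.

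**Power for one marker in one arm (n = 100).** Power = Φ(atanh(r)√97 - 1.96) for the continuous score; the cut replaces r by k·r.

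| r | Continuous | Cut, 50% response | Cut, 70% | Cut, 80% |
|---|---|---|---|---|
| 0.20 | 52% | 35% | 33% | 28% |
| 0.30 | 86% | 67% | 63% | 56% |
| 0.35 | 95% | 81% | 76% | 69% |

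**Power for a moderator (100 per arm).** Power = Φ(2·atanh(d/2)√(97/2) - 1.96), where d is the between-arm difference in correlation. The formula takes the two correlations as equal and opposite. At d = 0.4, power is 81% continuous, against 61% with the cut at 50% response and 57% at 70%.

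**Simulation check.** With N = 200, r = 0.2 and 20,000 replicates, power is 81-82% continuous, against 62%, 57% and 51% with the cut at 50, 70 and 80% response.

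**Can a response call be recovered by thresholding the predicted score?** Predicted scores shrink to the mean. At 70% response and r = 0.3, the share predicted as non-responders is 1 - Φ(0.524/0.3) = 4%, although 30% are non-responders, and only 7% of true non-responders are identified. A logistic model fitted directly to response and cut at a probability of 0.5 behaves almost identically (4% predicted, 7-8% identified). The weakness lies in hard classification from a weak marker, not in the continuous target.

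**The case against.** The strongest reply concerns scope. The binary definition stands in one parenthesis about machine learning, which is applied alongside conventional methods. The platforms are also analysed by methods described in a source not shown here, and those analyses may well use continuous scores. A reader might infer that the whole biomarker predictor and moderator aim loses this much information. The article does not support that, because it states no outcome scale for those analyses. This part of the reply stands.

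A reader might also infer that every randomized participant has an end-of-phase score. The planned dropout rules that out; the statement holds only for those assessed at the end of the phase.

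Response is also a reasonable thing to predict: it is the primary endpoint, it directs patients to crossover or maintenance, and the Background speaks of the likelihood that a patient will respond. This stands as a reason to keep a response prediction, but not as a reason to train only on the cut.

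The efficiency figures describe one marker under normal theory, not a multivariable classifier. That also stands: they show direction and rough size.

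Finally, a condensed article may leave modelling detail to the full protocol or analysis plan. That would answer silence about the target. Here the article states the target, and introduces it as a definition rather than as an example.

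**Conclusion.** The concern holds for the machine-learning prediction target as defined. Over the article's 50-80% ECT response range, the cut costs roughly 36-51% of the information about a single marker (36-42% at 50-70%), and power at r = 0.3 with 100 patients falls from 86% to 56-67%. This rests on a normal latent outcome, one weak-to-moderate linear marker, and the ECT range standing in for response rates that the plan does not give. For multivariable machine learning it is an approximation. The primary non-inferiority analysis is unaffected.

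**What to change.** In the prediction sentence of Data analyses:
- Name the continuous end-of-randomized-phase MADRS, adjusted for baseline MADRS, as the main target for predictor and moderator models, and keep response/non-response as a supportive target.
- Derive the response prediction as a probability from the continuous model's predictive distribution, not by applying the response criteria to the predicted score.
- Report AUC and calibration of that probability against observed response.

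No new data are needed. The cost is a sentence, some additional analysis and the calibration check, which matters because the derived probability depends on the model's residual distribution.
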